## Abstract

**Background:**

Meta-analyses of studies on psychological treatment of refugees describe highly varying outcomes, and research on multi-facetted and personalized treatment of refugees with post-traumatic stress disorder (PTSD) is needed. Music therapy has been found to affect arousal regulation and emotional processing, and a pilot study on the music therapy method Trauma-focused Music and Imagery (TMI) with traumatized refugees resulted in significant changes of trauma symptoms, well-being and sleep quality. The aim of the trial is to test the efficacy of TMI compared to verbal psychotherapy.

**Methods:**

A randomized controlled study with a non-inferiority design is carried out in three locations of a regional outpatient psychiatric clinic for refugees. Seventy Arabic-, English- or Danish-speaking adult refugees (aged 18–67 years) diagnosed with PTSD are randomized to 16 sessions of either music therapy or verbal therapy (standard treatment). All participants are offered medical treatment, psychoeducation by nurses, physiotherapy or body therapy and social counseling as needed. Outcome measures are performed at baseline, post therapy and at 6 months’ follow-up. A blind assessor measures outcomes post treatment and at follow-up. Questionnaires measuring trauma symptoms (HTQ), quality of life (WHO-5), dissociative symptoms (SDQ-20, DSS-20) and adult attachment (RAAS) are applied, as well as physiological measures (salivary oxytocin, beta-endorphin and substance P) and participant evaluation of each session.

**Discussion:**

The effect of music therapy can be explained by theories on affect regulation and social engagement, and the impact of music on brain regions affected by PTSD. The study will shed light on the role of therapy for the attainment of a safe attachment style, which recently has been shown to be impaired in traumatized refugees. The inclusion of music and imagery in the treatment of traumatized refugees hopefully will inform the choice of treatment method and expand the possibilities for improving refugee health and integration.

**Trial registration:**

ClinicalTrials.gov ID number NCT03574228, registered retrospectively on 28 June 2016.

**Electronic supplementary material:**

The online version of this article (10.1186/s13063-018-2662-z) contains supplementary material, which is available to authorized users.

## Background

Currently, there are more than 21 million internationally displaced refugees in the world, 3.5 million of them living in Europe [1]. The mental health problems and psychosocial strain in refugees resettled in Western countries has been suggested to relate to traumatic experiences and stress while living under war, persecution and other life-threatening circumstances, danger and challenges during flight, as well as post-migration experiences such as insecure waiting periods during asylum and family reunion procedures, poverty, lack of social support, acculturation difficulties and discrimination [2]. Reviews of studies on refugee health document a large variation in health status related to country of origin, country of resettlement and the methodological quality of the studies. In a systematic review of 20 surveys including 6743 adult refugees from seven countries a 9% prevalence of PTSD (99% CI 8–10%) was found, which is about ten times the rates in the age-matched general populations in the same countries [3]. In a systematic review of 29 studies including 16.010 war-affected refugees, significant between-study heterogeneity in prevalence rates of post-traumatic stress disorder (PTSD) (4–86%), unspecified anxiety disorder (20–88%) and depression (range 2–80%) was identified, although prevalence estimates typically were in the range of 20% and above [4]. All three disorders were associated with greater exposure to pre-migration trauma and post-migration stress, while depression was particularly associated with poor socio-economic status. In a study of 142 newly arrived asylum seekers in Denmark 34% had symptoms corresponding with the PTSD diagnosis [5].

In *International Classification of Diseases* (ICD-10) criteria for PTSD are the exposure to an exceptionally threatening event of catastrophic nature and demonstrating the symptom triad (1) intrusive trauma-related imagery or nightmares, (2) avoidance of situations that reminds them of the trauma and (3) either (a) partial amnesia of the trauma or (b) prolonged hypervigilance that causes irritability or frequent outburst of anger, concentration problems, sleeping problems and/or exaggerated startle response (F43.1, World Health Organization (WHO) ICD-10). In addition, PTSD influences cognitive abilities such as memory and learning, and often causes social withdrawal, all of which affect quality of life in a profoundly negative way, making it harder for the affected individuals to achieve successful integration and self-perseverance, including the adherence to study and work. In the upcoming ICD-11 the diagnosis Complex PTSD will be included, a diagnosis for additional symptoms related to longitudinal and/or severe traumatic exposure characterized by disturbances in emotional regulation and relational capacities, dissociation, somatic distress and alterations in belief systems [6]. In the draft for the upcoming ICD-11 the following symptoms are listed: (1) severe and pervasive problems in affect regulation; (2) persistent beliefs about oneself as diminished, defeated or worthless, accompanied by deep and pervasive feelings of shame, guilt or failure related to the traumatic event; and (3) persistent difficulties in sustaining relationships and in feeling close to others (ICD-11, draft version). In line with that, insecure attachment recently has been shown to be common in refugees [7, 8]. Furthermore, refugees from non-Western countries show high levels of unexplained somatic symptoms that potentially can be explained by traumatization, the results of torture and that also might be a culturally accepted way to express psychological pain taking into consideration the stigmatization of psychiatric care [9]. The increased number of refugees with severe mental health problems necessitates the development of effective treatment modalities.

### Research on refugee treatment

Standardized short-term treatment has been shown to be effective in the treatment of single-trauma PTSD without significant comorbidity [10, 11]. However, simple PTSD is not typical in traumatized refugees, where complex trauma and comorbidity is common. The recommendation from leading trauma researchers in complex PTSD is a treatment based in a cross-disciplinary setup with a phased psychotherapeutic component of a duration of several years [6].

Until today the evaluation of psychological treatment modalities of traumatized refugees has mostly focused on individual cognitive behavioral therapy (CBT) and narrative exposure therapy (NET), with some studies in eye movement desensitization reprocessing (EMDR), combined methods/interdisciplinary treatment and group treatment. Compared to other patient groups, the evaluation of psychotherapeutic treatment of refugees can be difficult, randomized controlled trials are few and sample sizes are generally small. There are many possible explanations for this. Many refugees that have experienced traumatic events, such as persecution, are reluctant to trust authorities, including healthcare personal. The complexity of trauma symptoms, acculturation difficulties and the influence of the translator upon the psychotherapeutic relationship also have to been taken into account.

In a Cochrane review evaluating nine studies on CBT and NET with torture survivors, no effect was found immediately after treatment. However, at 6 months’ follow-up, four out of nine studies showed a medium effect on trauma symptoms [12]. Slobodin and de Jong [13] performed a meta-analysis of studies with quantitative pre-post intervention measurement of trauma symptoms, including refugees and asylum seekers. They found positive effects on PTSD symptoms after treatment with CBT and NET in certain refugee populations. Other intervention studies, i.e., EMDR, psychodynamic interventions, family interventions, group interventions, pharmacological treatment and combined methods/interdisciplinary treatment, were limited by methodological considerations, such as lack of randomization, absence of control group and small samples. Similar conclusions were found in previous academic literature reviews [14–17]. Palic and Elklit [17] reviewed 25 refugee studies and found that the effect of different approaches varied from very small to medium effect sizes. Among the reviewed studies a few demonstrated very large effect sizes on PTSD symptoms after trauma-focused phased CBT with a body-oriented and culturally sensitive approach. In these approaches CBT was combined with guided imagery with culturally specific images such as a flowering lotus [18–20] or cognitive restructuring was combined with progressive relaxation, affect regulation skills and guided imagery, such as imagination of a safe place [21]. These approaches seem to resemble the music therapy method applied in the present clinical trial.

Lambert and Alhassoon [22] aggregated the effect sizes for trauma symptoms and depression in 13 randomized controlled trials of different psychotherapeutic interventions for traumatized adult refugees. They found a large aggregate effect size for PTSD that was independent of type of outcome measure (Hedges’ *g* .91, *p* .001, 95% CI [.56, 1.52]. Depression was assessed in nine studies, and here the effect size was also large (Hedges’ *g* .63, *p* .001, 95% CI [.35, .92]. Higher number of sessions (3–12) predicted the magnitude of PTSD change significantly. Translated and untranslated sessions were compared and there was no visible effect of the translation process upon the clinical outcome of the studies.

Because of the complex situation of traumatized refugees and the fact that the majority of refugees remain chronically traumatized, several of the reviews maintain, that other measures than the level of trauma symptoms have to be recognized when evaluating the effect of specific therapies in this patient group. These include the evaluation of long-term treatment effects, social functioning, improvements in the capacity for maintaining meaningful relationships, and a positive experience of identity and meaning [13, 17]. Recently, the investigation of attachment-based treatment strategies, and the inclusion of attachment style as outcome measure has been recommended [7, 8]. Furthermore, treatments that could prove effective in preventing relapse should be further investigated. These include methods that address affect dysregulation and coping strategies targeted to the ongoing insecurity and uncertainty typical for the life situation of refugees [16, 17]. Personalized treatment is currently being introduced in many psychiatric clinics. In line with that Slobodin and de Jong [13] argued that it is necessary to devise the treatment of refugees individually from a spectrum of possibilities.

#### Physiological measures and PTSD

Levels of stress hormones, such as cortisol have been widely used to measure the stress response in PTSD patients. However, several studies have failed to confirm the expectation that cortisol is elevated in PTSD. On the contrary, patients who suffer from PTSD generally have normal levels of cortisol, and often their levels are even lower than the values of healthy participants [23, 24]. It has been supposed that the HPA axis suppresses the cortisol response in PTSD (or vice versa), making this hormone difficult to use as an outcome measure in trials [25].

Oxytocin is a neuropeptide that is involved in the regulation of fear. It also enhances trust and prosocial behavior, and it has been associated with stress reduction, wound healing, attachment, calmness and rest [26]. It has even been suggested that oxytocin could be administered intranasally in the treatment of PTSD, especially it has been considered for early prevention, and as a treatment to increase social responsiveness [27, 28].

In a meta-review of 400 studies investigating the effect of music on brain chemistry, it was found that music contributes to the production of peptides such as oxytocin, vasopressin and dopamine that add to the creation of social bonding, and endogenous opioids that contribute to the maintenance of steady social relationships [29]. A number of music intervention studies have demonstrated increased peripheral oxytocin levels after post-operative music listening [30], singing lessons or improvised singing [31–33] and choir singing [34]. Beta-endorphin is also associated with the stress response and low levels have been implicated in PTSD [35]. Beta-endorphin was lowered in healthy undergraduates after music and imagery [36] and in patients with coronary heart disease after music listening [37].

### Research on music therapy with refugees

For decades, music therapy as a clinical psychotherapy model has been applied to a broad spectrum of populations in the health system [38]. Recent Cochrane reviews of music therapy treatment have demonstrated moderate-quality evidence on reduction of depression in people with dementia [39] improvement of walking in people with stroke [40] and increase of social communication skills in children with autism [41]. In a Cochrane review of people with schizophrenia, it was concluded that music therapy as an addition to standard care improved global state, mental state (including negative symptoms) and social functioning [42]. A selective review of music therapy studies with PTSD patients concluded that individual and group interventions seem to reduce core PTSD symptoms and depression and increase social function, hope and resilience in both adults and children [43].

A randomized controlled study including adult psychiatric patients with persistent PTSD, who had been unable to benefit from CBT, showed a significant decrease of all dimensions of PTSD symptoms after group music improvisation compared to a waitlist control [44]. Studies in group music therapy with children and adolescents showed some effect on PTSD symptoms after four sessions of songwriting compared to games in nine psychiatric patients aged 9–17 years with histories of sexual abuse [45]. Two Australian school studies demonstrated beneficial effects of music therapy: In 31 newly arrived refugees, a decrease in hyperactivity, aggressive behavior, depression, anxiety and somatization were found in periods with music therapy compared to periods without music therapy [46]. In a randomized study, reduction of depression, hopelessness and anxiety after group music therapy compared to art classes was demonstrated (*n* = 18) [47, 48].

Jespersen and Vuust [49] found significant improvement of sleep quality in a randomized controlled trial of adult refugees with undiagnosed PTSD (*n* = 23). All participants slept on a special pillow with loudspeakers; one group listened to calming music 30 min before falling asleep, the other group had no music. In another sleep study, music-guided relaxation resulted in decreased depression and increased sleep quality compared to relaxation with no music in 13 veterans [50]. Akhtar [51], adapting a quasi-experimental design, found beneficial changes in depression and anxiety in a small group of Pakistani traumatized refugees after music listening to live improvised music (in combination with treatment as usual). Likewise, Alanne [52] found improvements in depression and quality of life in follow-up case studies of three torture survivors. Using a factor analysis of 106 sessions he demonstrated improvement in the ability of the refugees to contain, process and contain emotions and traumatic events from before to after music listening [52].

#### Guided Imagery and Music (GIM)

The Bonny method of GIM is facilitating music-evoked imagery in an altered state of consciousness as an in-depth psychotherapeutic method. The original method applies 30–45 min of listening to carefully selected movements of classical Western music [53, 54]. Adaptations of the method to trauma survivors have been promising. In a naturalistic study of 102 women suffering from Complex PTSD, 50 h of GIM resulted in significant improvement of PTSD symptoms, decreased symptoms of dissociation and better “sense of coherence” with large effect sizes compared to PITT (imagery-based therapy without music) [55]. In psychiatric patients, GIM in group treatment conveyed restitution and increased affect regulation [56, 57] and reduced trauma symptoms [58]. In a psychiatric group treatment program, including patients with refugee background, the outcome measures showed better outcomes of GIM in trauma victims than in patients without trauma history [59]. Two pilot studies with trauma survivors demonstrated large effect sizes of GIM interventions. In one study, ten women with histories of sexual/physical childhood abuse who suffered from complex or single PTSD participated in 12 sessions of trauma-focused group GIM. All of the participants achieved significant symptom relief of PTSD symptoms, dissociation, anxiety and depression [60]. In another study, the effect of ten sessions of individual resource-oriented GIM was assessed in female veterans, who had been subjected to sexual abuse. Focus group interview analysis found that music therapy succeeded in helping the victims cope with their PTSD symptoms, regulate their emotions, decrease arousal, express repressed emotions and connect better with others. Creative processing (drawing the imagery) provided increased creative expression and a way to continue processing between sessions [61].

### Pilot study

The background for the present study is a completed feasibility study in the form of a pilot project concerning treatment of traumatized refugees with PTSD in Region Zealand, Denmark [62]. In the 1-year-long project, an adaptation for trauma treatment of GIM called Trauma-focused Music and Imagery (TMI) including the central elements music listening and imagery was applied to 16 adult participants. Participants were ten men and six women of different origin (Syria, Afghanistan, Iraq, Iran) with a mean age of 40 years. All participants completed the 16 sessions, but weekly sessions were not always possible due to cancellations; therefore, length of treatment was on average 26 weeks. The single group pre-test/post-test study showed significant positive changes with large effect sizes (0.81–1.17) on PTSD symptoms, well-being, sleep quality and social function. Symptom load measured with the Harvard Trauma Questionnaire, showed both significant change (*p* < 0.002) and large effect size (1.15). Three participants scored under cutoff for PTSD after treatment. Patient satisfaction was measured with a 7-point smiley scale from “very dissatisfied” to “very satisfied.” The average score was 5.5 with a slightly higher satisfaction towards the end of treatment. According to post-treatment interviews the patients experienced improvement as a result of treatment, and they experienced music as important for coping and emotional regulation. Furthermore, the music influenced the restoration of trust and hope, both of which are known to be involved in the achievement of secure attachment. The music repertoire used included Arabic and Afghan pieces, as 25% of the participants needed familiar music to work with their inner images. All participants used the music method at home for self-care, relaxation, affect regulation, release of pain symptoms, and positive focusing.

In order to assess the positive outcome of the pilot study in a larger study, the randomized clinical trial that is presented here was established.

### Rationale for the randomized trial

The increased number of traumatized refugees and their generally problematic situation cause pressure on the treatment systems in the host countries. Accordingly, effective treatment options are needed in order to help the refugees to attain positive integration and a better quality of life. To our knowledge, no former randomized studies on music therapy with adult refugees exist, and no known refugee studies include physiological measures. The study hereby contributes to the investigation of music therapy and the GIM method as an effective treatment modality. Verbal psychotherapy carried out by psychologists is chosen as comparator because it is the standard treatment modality in the field, and because the effect of music therapy versus verbal therapy can be investigated. Due to the limited evidence and knowledge about the efficacy of existing treatment programs on key symptoms related to the complex traumatizing of refugees, including unsafe attachment patterns and dissociation, the study attempts to add to the knowledge of the efficacy of both.

## Methods

### Aim

The aim of the study is to create increased treatment modalities for refugees with PTSD, and to provide new knowledge about the efficacy and non-inferiority of music therapy compared to standard verbal psychotherapy as primary psychotherapeutic methods in refugee treatment. The study also seeks to point out possible parameters that can aid as a help in the clinical referral procedure and guide the choice of one or the other treatment modality.

Furthermore, the study aims to investigate the change of symptoms on several parameters that earlier have been tested in a pilot study as well as parameters that have not been tested before (dissociation and attachment). As an extension of the study, molecular data (salivary oxytocin, beta-endorphin and substance P levels) are included as possible outcome measures.

### Research questions

The following research questions are posed:Will music therapy (TMI) be as effective as standard treatment regarding the decrease of TSD symptoms (primary outcome) from pre to post treatment and from pre-treatment to 6 months’ follow-up?Will music therapy (TMI) be as effective as standard treatment regarding the decrease of dissociation and the improvement of attachment style and well-being (secondary outcomes) pre to post treatment and from pre-treatment to 6 months’ follow-up?Does any variable from the patient data at baseline (i.e., gender, age) specifically correlate with good outcomes of music therapy on trauma symptoms compared to standard treatment?Concerning patient satisfaction with therapy sessions, is there a difference between music therapy and verbal therapy, and is there any development in the assessment of the sessions during the therapy course?Will basic levels of salivary oxytocin, beta-endorphin and substance P be changed by the treatment, are any changes stable at follow-up, and are there differences between the two groups?Will the levels of salivary oxytocin, beta-endorphin and substance P be affected by one session, and are there a difference between the groups, and between a session at the beginning and in the end of treatment?

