### Trial design

The research design is a randomized clinical trial with a parallel-group design including two intervention groups: music therapy (Trauma-focused Music and Imagery (TMI)) and standard psychological treatment. We use a non-inferiority framework, where we test whether or not music therapy is inferior to standard treatment. We intend to allocate 70 adult refugees diagnosed with PTSD. Repeated measures take place at baseline, post therapy and at 6 months’ follow-up. A short form of the primary outcome measure is also collected twice during the treatment period (session 5 and 10). Session evaluation from clients is collected after each session. Saliva samples are collected at baseline, post therapy and follow-up, and also pre and post sessions 4 and 14 (see the Standard Protocol Items: Recommendations for Interventional Trials (SPIRIT) flow chart; Fig. 1). All dimensions of the study protocol have been described adhering to the SPIRIT Checklist (Additional file 1). We also adhere to the revised Consolidated Standards of Reporting Trials (CONSORT) guidelines [63].

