## Outcome measures

The primary outcome measure is the therapist-administered Harvard Trauma Questionnaire (HTQ) [71], demonstrating an acceptable reliability in different languages, including Arabic [72, 73]. The first 16 items of part IV are used, describing to which degree the participants felt disturbed by trauma symptoms corresponding with the PTSD diagnosis in DSM-IV. The scale has three subscales: avoidance, hypervigilance and intrusion.

Eight of the HTQ questions are included in the scale PTSD-8 [74], which is administered at the beginning of sessions 5 and 10 (of 16 sessions) to monitor the effect on trauma symptoms during treatment.

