#### Power calculation

In order to estimate the level of power we reviewed randomized and non-randomized trials where refugees suffering from PTSD were treated with stabilization and trauma exposure strategies with cognitive and narrative elements corresponding to the standard treatment in our study, and where the Harvard Trauma Questionnaire was used to measure changes in trauma symptoms (the primary outcome in the current study). The variations in the studies were considerable, and we chose to only look at studies that had a number of sessions that were similar to the current study, and where the mean baseline value of HTQ were around 3.3, a value that we found to correspond to our population in the pilot study [18, 62, 83–86]. Non-significant differences between 0.1 and 0.5 was found in HTQ from pre to post treatment. Based on our clinical experience and data from these studies, we estimate a clinical insignificant difference of 0.3 as the maximal difference between music therapy and standard treatment to confirm the non-inferiority hypothesis. A mean standard deviation of 0.48 on post-scores of HTQ was calculated from the studies referred above.

The power calculation was based on a significance level of 0.05, power 0.08, *d* = 0.3 and *SD* = 0.48. The calculation was carried out with software from Epi-info 7 (http://wwwn.cdc.gov/epiinfo/) in cooperation with Department for Statistics, Psychiatric Research Unit, Region Zealand and PFI.

The result indicates a minimum of 64 participants (32 in each group).

Adherence to music therapy has been found to be good in psychiatric patients with a low dropout rate (11.5%) [87]. In three former randomized clinical studies on psychological treatment of refugees with large samples low dropout rates (7–10%) were demonstrated at follow-up [21, 83, 88].

We have, therefore, chosen to include a dropout rate of 10% and thus end up with *n* = 70 (35 in each group).

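### The primary non-inferiority question is posed at two time points, but the sample size covers one test and no section says which time point decides

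*Protocol article*

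**What the plan says.** All references are to the protocol article.

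- **Research questions.** The first question marks PTSD symptoms as the primary outcome and asks about "the decrease of TSD symptoms (primary outcome) from pre to post treatment and from pre-treatment to 6 months" of follow-up. The two periods are joined by a plain conjunction.
- **Trial design.** "We use a non-inferiority framework, where we test whether or not music therapy is inferior to standard treatment". Measurements are listed at baseline, after therapy and at 6 months, with none singled out.
- **Hypotheses.** No time point is attached to the non-inferiority hypothesis.
- **Outcome measures.** "The primary outcome measure is the therapist-administered Harvard Trauma Questionnaire (HTQ"). The instrument is named but not the time point.
- **Statistical methods.** The primary outcome goes into an ANCOVA over five measuring points. The contrast to be set against the margin is not identified.
- **Power calculation.** The margin: "we estimate a clinical insignificant difference of 0.3 as the maximal difference between music therapy and standard treatment to confirm the non-inferiority hypothesis". Its source data: "Non-significant differences between 0.1 and 0.5 was found in HTQ from pre to post treatment". The SD: "A mean standard deviation of 0.48 on post-scores of HTQ was calculated from the studies referred above". The settings: "The power calculation was based on a significance level of 0.05, power 0.08". The result: "The result indicates a minimum of 64 participants (32 in each group"), raised to 70 for dropout.

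**The concern.** The primary question and the sample size do not match: two comparisons are asked and one is sized. The sizing inputs all belong to the end of treatment, yet the article never calls that the primary time point, and the first research question gives 6 months equal standing.

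The consequence depends on a rule the reader has to guess. If non-inferiority must be shown at both times, the trial has less power than a single-test calculation implies. If one time is enough, the chance of a false non-inferiority claim rises. If the results split, there is no agreed reading.

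The two tests are also not interchangeable. Under Procedures, Potential harms and Risk of bias, participants who need further psychotherapy, or who leave music therapy for standard treatment, are excluded from follow-up measurement. The 6-month comparison therefore rests on a smaller and selected group.

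**Working it through.** **Inputs from the Power calculation section:** margin 0.3 HTQ points, SD 0.48, significance level 0.05, 32 per arm. **Inferred:** one-sided testing, 80% power, true difference 0. **Assumed, because the article gives no value:** correlation ρ between the two test statistics, 0.5 to 0.8; correlation r between baseline and outcome, 0.3 or 0.5.

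**1. Reproduce the plan's figure.** n per arm = 2 × SD² × (z₁₋α + z₁₋β)² / margin².
- One-sided 5%, 80% power: 2 × 0.2304 × (1.645 + 0.842)² / 0.09 = 31.7, so 32 per arm and 64 in total. This matches.
- One-sided 2.5%, 80% power: 40.2, so 41 per arm and 82 in total. This does not match.
- Power taken literally as 0.08 gives 1 per arm, so 0.08 is a misprint of 0.80.

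**2. Power of one test at 32 per arm.** SE = 0.48 × √(2/32) = 0.12. Margin/SE = 2.5. Power = Φ(2.5 − 1.645) = Φ(0.855) = 80.4%.

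**3. Both time points must succeed.** The error rate stays at or below 5%. Power is the bivariate normal probability that both statistics pass, each with threshold 0.855:
- ρ = 0.5: 69.2%
- ρ = 0.8: 73.4%
- Over the wider range ρ = 0 to 0.9: 64.6% to 75.4%

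**4. The same rule with baseline adjustment.** The adjusted SD is 0.48 × √(1 − r²).

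| r | adjusted SD | single test | both, ρ = 0.5 | both, ρ = 0.8 |
|---|---|---|---|---|
| 0 | 0.480 | 80.4% | 69.2% | 73.4% |
| 0.3 | 0.458 | 83.5% | 73.7% | 77.3% |
| 0.5 | 0.416 | 89.3% | 82.1% | 84.7% |

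**5. Extra loss at 6 months.** The article gives no number. As an illustration, with 28 per arm at follow-up and 32 at post-treatment, unadjusted power for both is 65.9% (ρ = 0.5) to 70.2% (ρ = 0.8).

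**6. Either time point suffices.** With the true difference equal to the margin at both times, the chance of at least one false success is 1 − P(both statistics below 1.645):
- ρ = 0.5: 8.8%
- ρ = 0.8: 7.5%

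**7. Split results.** With truly equal treatments and the unadjusted figures, exactly one of the two tests passes with probability 2 × (single − both): 2 × (80.4 − 69.2) = 22% at ρ = 0.5, and 2 × (80.4 − 73.4) = 14% at ρ = 0.8.

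**The case against.** The strongest reply is that nothing is miscalculated. The margin evidence and the SD come from pre-to-post data, so post-treatment is the working primary time point and 64 is right for it. A list of research questions is not a decision rule, and the question on secondary outcomes uses the same two-period wording. Much of this stands: on that reading the sample size needs no change and the defect is a missing label. But the article never supplies the label, and its only sentence tying the primary outcome to time names both periods.

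A second reply is that error allocation and the reading of split results belong in an analysis plan that is not shown. That is fair for the mechanics. It does not cover the choice of primary time point, because the sample size stated in this article depends on it.

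Three stronger readings are tempting and are not supported:

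- A reader might infer that the 5% error rate is already broken. No section says that success at either time is enough, and the wording points to both, under which the error rate holds.
- A reader might infer that power certainly falls below 80%. The planned analysis is an ANCOVA, and with a baseline correlation of 0.5 the power for both tests exceeds 80% before extra loss. The power calculation takes no credit for adjustment, so this is possible but not shown.
- A reader might see biased scoring, since music therapists run the research procedures. The Blinding section has HTQ scored after treatment and at follow-up by external psychologists unaware of allocation, with data concealed until the trial ends, and Auditing denies researchers access before data collection ends. These safeguards protect the measurements; they do not settle which time point decides.

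**Conclusion.** The point holds as a mismatch between the stated primary question and the stated sample size. The calculation supports one test, and the article does not say which of two time points that test is. Under the natural reading that both must succeed, unadjusted power is about 69–73%, with 74–77% or 82–85% after baseline adjustment at r = 0.3 or 0.5, and less if follow-up exclusions are material. The 7.5–8.8% false non-inferiority rate would apply only under an either-time rule that the article does not contain.

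These figures rest on normal approximations, equal SDs and a true difference of zero at both times for power, one-sided 5% testing inferred from the reproduced 64, and assumed values of ρ and r. If post-treatment alone is confirmatory, 64 stands. The matter should be fixed, but it does not invalidate the design.

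**What to change.** Before the data are opened:

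1. In Research questions and Statistical methods, name HTQ at post-treatment as the single confirmatory non-inferiority test against the 0.3 margin.
2. In Statistical methods, state that HTQ at 6 months is tested for non-inferiority only if the post-treatment test succeeds. This fixed sequence needs no split of the error rate, and it gives a split result an agreed reading.
3. In Power calculation, state that the 64 participants and the 80% power apply to the post-treatment test only. State the one-sided 5% level if that is what was used, and correct the printed 0.08.

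Post-treatment is proposed because the plan's own sizing uses it. The Background reports a review that found no effect immediately after treatment and a medium effect at 6 months in four of nine studies, so the sponsor may prefer 6 months; in that case the margin, the SD and the loss allowance need to be justified for that time point.

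The cost is a few sentences, a 6-month claim that becomes conditional, and the committee approval and registry update described under Protocol amendment. No extra patients or data are needed.
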